##### Data collection

Data will be collected by the study team preoperatively, intraoperatively, and at multiple time points postoperatively (directly postoperative at the recovery room, 1 postoperative day, 7 postoperative days, or day of discharge, whichever comes first) (Fig. 2). The data collection includes the baseline patients’ characteristics, including blood pressure measurements, renal function markers, and cardiac biomarkers as mentioned before. The intraoperative data will be collected from the HemoSphere monitor, which will collect all hemodynamic data every 20 s, and the electronic patient data management system (NarkoData Version 4.17.12.23066, IMESO, Gießen, Germany). All data will be collected in an electronic database on the university hospital server and will be only available for the study team members.

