### Preoperative management

Patients are recruited before surgery after checking inclusion and exclusion criteria by the dedicated study team. Informed consent is obtained at this time from a study team member. Patients will be randomized 1:1 to the two groups after achieving the patient’s informed consent. Randomization will be performed using computer-generated random numbers and will be performed by the study team. Further, the following basic characteristics are obtained:Age, sex, height, weight, ASA scorePre-existing conditions (hypertension, coronary heart disease with and without history of myocardial infarction, peripheral arterial disease, renal failure, chronic obstructive pulmonary disease, diabetes)Previous major surgeriesCurrent prescription of medicationFurthermore, the following laboratory results will be gained:Blood cell countGlobal coagulatory function (internationalized ratio, thromboplastin time, fibrinogen levels)Parameters of renal function (creatinine, urea,)Parameters of cardiac function (troponin I, creatinine kinase, myoglobin, nt brain natriuretic peptide)Inflammatory Parameters (C-Reactive Protein, Procalcitonin)

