##### Intervention group

The intervention group will receive HPI-guided goal-directed therapy (GDT) using the ClearSight system. Prior to the surgery the rest cardiac index and contractility (dp/dt) will be quantified. For this purpose, the cardiac index will be measured in the preoperative night by applying the HPI ClearSight system through a study team member. If the rest cardiac index is not available throughout the night because the patient’s sleep is altered by the measurements, the awake cardiac index will be quantified until the monitoring is stopped for the night sleep of the patient. This mean baseline measurements (CI and dp/dt) will then be the target cardiac index throughout the study algorithm (Fig. 1). In case no sleep measurement is achievable, the awake measurement will be accounted as the baseline value. The perioperative study intervention period starts with the beginning of anesthesia and ends at the end of surgery. Intraoperative MAP will be maintained at least at 65 mmHg, and cardiac index and dp/dt will be individually optimized according to the GDT algorithm.

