**Fig. 3 Fig3:**
[figure not shown]
Calculation of AUC and TWA for intraoperative hypotension

Secondary outcome parameter are:

Composite endpoint: Occurrence of AKI according to KDIGO criteria during the hospital stay or until postoperative day 7and MINS: Defined as increased troponin levels that exceed the 99th percentile of the upper reference limit of the assay after measured directly postoperative, 1^st^ and 7^th^ postoperative day or day of discharge, whatever comes first.Incidence of delirium measured directly postoperative and on the 1^st^ postoperative day by the 3D-CAM Test [15]

Furthermore, intraoperative data, such as anesthesia and surgery time, volume of intravenous fluids (crystalloids, colloids, blood products, and autologous blood), blood loss, transfusion rate, type and dosage of vasopressors, and type and dosage of inotropic medication used during the procedure, were documented.

Finally, the length of hospital and ICU stay and hospital mortality were analyzed.

In addition to the predefined parameters, we will also retrospectively analyze variables related to overtreatment. In particular, we will calculate the area above threshold (AAT), defined as the cumulative time–pressure product with a mean arterial pressure above a threshold of 100 mmHg. This parameter will allow us to assess the extent of potential overtreatment in the intervention group compared to the control group.

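### The described division of tasks lets the 3D-CAM delirium rating be made by someone who knows the patient's arm, and no masking of raters is stated

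*Protocol article*

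**What the plan says.** All of the following is in the protocol article.

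- **Recruitment and allocation** (Preoperative management): "Patients are recruited before surgery after checking inclusion and exclusion criteria by the dedicated study team". The same section states "Randomization will be performed using computer-generated random numbers and will be performed by the study team".
- **Night recording** (Intervention group): "the cardiac index will be measured in the preoperative night by applying the HPI ClearSight system through a study team member". The Control group section describes no counterpart.
- **Data collection** (Data collection): "Data will be collected by the study team preoperatively, intraoperatively, and at multiple time points postoperatively". The postoperative times are "directly postoperative at the recovery room, 1 postoperative day, 7 postoperative days, or day of discharge, whichever comes first". The database is open to study team members only.
- **Delirium** (Outcome, secondary parameters): "Incidence of delirium measured directly postoperative and on the" first postoperative day, by the 3D-CAM. No rater is named. Reduced delirium is also a stated secondary hypothesis and a secondary objective.
- **Masking** (Abstract and Control group): in control patients the HemoSphere monitor is covered and its alarms silenced, so that the anaesthesiologist does not see the continuous values. The Discussion and Limitations return to this same arrangement. Nothing is said about masking the people who assess outcomes.

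**The concern.** The 3D-CAM is a bedside rating. The article names the tool without describing it; that it rests on interview and observation is general knowledge of the instrument. A rater who knows the arm, and expects the new technology to help, can tip borderline ratings. The first rating is the more exposed of the two, because it is made when patients have just come out of general anaesthesia.

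The team that would naturally do this rating is also the team that holds the allocation and has spent part of the preoperative night with intervention patients. If raters do know the arm, an observed difference in delirium cannot be separated from rater expectation. A larger sample would not help, since it reduces random error and leaves this bias in place.

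The exposure is specific to delirium. The primary endpoint is computed from pressures that the monitor stores every 20 seconds in both arms. MINS is a troponin threshold, and AKI is classified by KDIGO criteria, for which the plan collects renal function markers.

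**Working it through.** The plan states no figure on this point, so there is none to reproduce. The check is to trace who does what, and then to illustrate size under stated assumptions.

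**Step 1: roles set side by side**

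| Task | Who, according to the article | Reveals the arm? |
|---|---|---|
| Screening and consent | study team | no, it precedes allocation |
| Randomisation | study team | yes |
| Preoperative night recording | a study team member | yes, if done only in the intervention group, as its placement suggests |
| Postoperative data, including recovery room and day 1 | study team | outcome side |
| 3D-CAM, directly postoperative and day 1 | not named | outcome side |

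The 3D-CAM times coincide with the first two postoperative collection times, and the study team is the only group to which postoperative data collection is assigned. That the team also rates the 3D-CAM is an inference from these two facts. No sentence separates the allocating members from the rating members, and none withholds the allocation from a rater.

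**Step 2: a single example**

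Assume 11 of 75 patients are truly delirious in each arm (11/75 = 14.7%). Suppose three borderline control patients are rated positive and three borderline intervention patients negative.

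- Control: 11 + 3 = 14, and 14/75 = 18.7%.
- Intervention: 11 − 3 = 8, and 8/75 = 10.7%.
- Apparent relative reduction: 1 − 8/14 = 42.9%, with no true effect.
- Two-sided Fisher's exact test: p = 0.25, not significant.

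The example shows a distorted estimate, not a false positive test.

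**Step 3: effect on the planned test**

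Inputs from the article are Fisher's exact test at two-sided 0.05 (Statistical analysis), and 75 enrolled or 66 evaluable per arm (Sample size calculation). Assumed inputs are a true delirium rate p equal in both arms, and a fraction m of intervention-arm cases not recorded. The observed rates are then p in controls and p(1 − m) in the intervention arm. The probability of a significant result is the sum, over all pairs of case counts with Fisher p < 0.05, of the product of the two binomial probabilities.

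| Per arm | m | p = 10% | p = 20% | p = 30% |
|---|---|---|---|---|
| 75 | 0 | 2.7% | 3.1% | 3.3% |
| 75 | 25% | 4.6% | 8.6% | 13.7% |
| 75 | 50% | 12.8% | 32.3% | 52.7% |
| 66 | 0 | 2.4% | 3.1% | 3.2% |
| 66 | 25% | 3.9% | 7.9% | 12.1% |
| 66 | 50% | 10.4% | 28.2% | 46.9% |

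With misrating present, nearly all of these false positives favour the intervention. At 75 per arm, p = 20% and m = 25%, for example, 8.4 of the 8.6 percentage points do. At a 10% rate with a quarter of cases missed, the error rate stays below 5%.

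**The case against.** The strongest objection is that the point rests on silence in a condensed article. Protocol version 1.1, the SPIRIT checklist and the data collection figure are not shown, and any of them may name a masked rater. Study team is a collective term: nobody is said both to randomise and to rate. The Data collection section does not mention the 3D-CAM, and the Outcome section gives its timing without a rater. The statement on database access concerns confidentiality and does not say that every member sees the allocation. The finger cuff is worn in both arms, so it is a weak cue to the arm. The numerical illustrations rest on assumed rates and assumed misrating.

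Most of this stands, and it rules out a stronger reading. A reader might infer that delirium is in fact rated unmasked, or that one person allocates and rates. The article does not say so. A reader might also take the 43% in the example as an expected bias. It follows entirely from the six patients assumed to be reclassified, and it is not significant by the planned test.

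What does not stand is that nothing needs changing. The article does describe its masking and does assign these tasks. Under that description the masking covers only the control-arm anaesthesiologist, and the team holding the allocation is the only one assigned postoperative data collection. The Limitations section acknowledges bias from unequal information, but only in clinical management, not in outcome rating.

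**Conclusion.** The point holds as a weakness in the described arrangement, not as evidence of unmasked rating. As written, the plan allows the 3D-CAM to be scored by someone who knows the arm, which could bias this one secondary endpoint. The conclusion rests on two inferences: that the study team performs the 3D-CAM, and that the night recording is made only in the intervention group.

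No size can be derived from the document. Under the assumptions above, the false positive rate for delirium at 75 per arm runs from 4.6% (10% true rate, a quarter of intervention-arm cases missed) to 52.7% (30% true rate, half missed). The upper end needs strong misrating. The trial's primary conclusion is little affected. The point is worth acting on because the remedy is cheap and delirium is a named hypothesis.

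**What to change.** State who rates the 3D-CAM. In the recovery room and on day 1, this should be an existing study-team member who took no part in that patient's randomisation, night recording or theatre care, and who has no access to the allocation or the anaesthesia record. Record for each assessment whether the rater was masked.

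Recruitment began in July 2024 and was expected to finish around the end of 2025 (Trial status), so some or all patients may already have been assessed. Where this was done without masking, report delirium as assessed unmasked and interpret any difference accordingly. If masked rating is already in place, one sentence saying so settles the matter.

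The cost is some scheduling effort and a restriction on access to the allocation in the database. No extra staff are needed, and no endpoint, sample size or treatment changes.

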**Fig. 2 Fig2:**
[figure not shown]
Data collection

#### Outcome

The primary outcome is the incidence and severity of IOH in patients undergoing major trauma and orthopedic surgery. The severity of IOH will be quantified using the TWA of hypotension, defined as episodes where MAP remains below 65 mmHg for at least one minute. The TWA will be calculated as the area under the curve (AUC) for MAP values below 65 mmHg, normalized by the total duration of anesthesia. The AUC for MAP below 65 mmHg will be determined by multiplying the magnitude of deviation (in mmHg) below 65 by the duration (in minutes) of each hypotensive episode (see Fig. 3).

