**Methods/design:**

This monocentric, randomized, prospective interventional trial will be conducted at the University Hospital Giessen. The study will include patients aged 45 years and older undergoing major orthopedic or trauma surgeries. Participants will be randomized into two groups: an intervention group receiving hemodynamic management using the ClearSight system in combination with a HPI-based treatment algorithm and a control group receiving standard care. The patients from the standard group also receive continuous cardiac output monitoring; however, this will be blinded to the anesthesiologist, to ensure the comparability of the measured hemodynamic parameters. The primary endpoint is the incidence, duration and severity of IOH, which is defined as MAP < 65 mmHg for at least one minute and which is calculated as the area under MAP < 65 mmHg and the time-weighted average (TWA) of MAP < 65 mmHg. Secondary endpoints include the occurrence of postoperative AKI (measured by KDIGO criteria), MINS (measured by high-sensitivity troponin I assays), and postoperative delirium. The study aims to recruit 150 patients, accounting for potential dropouts, to provide sufficient power to detect differences in the primary and secondary endpoints.

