### Study hypotheses

#### Primary hypothesis

The perioperative use of non-invasive HPI-guided goal-directed therapy (GDT) reduces the incidence, and severity of IOH in patients undergoing major trauma and orthopedic surgery.

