### Study objectives

The primary objective is to investigate whether HPI-guided GDT can reduce the incidence, duration, and severity of IOH in comparison with no GDT. Secondary objectives include assessing the impact on postoperative renal failure, myocardial injury, and delirium.

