### Sample size calculation

The study aims to enroll 150 patients to ensure adequate power. The aim of the study is to show the impact of non-invasive cardiac output monitoring on the incidence of IOH in a cohort of trauma and orthopedic surgery. Sample size calculation was performed with regard to a study by Maheshwari et al. who investigated the effect of HPI on the prevention of hypotension [16]. This study was chosen because the primary endpoint, respectively the definition of hypotension (MAP < 65 mmHg), was identical to our study, and they investigated also non-cardiac surgical patients. In this study, the mean area under the curve of MAP ≤ 65 mmHg of patients without hemodynamic management accounted for 34.2 mmHg min (8.5–112.7) compared to 32.7 mmHg min (6.3–102) in patients with hemodynamic measurement. Aiming for an alpha of 0.05 and power of 0.95, the sample size calculation resulted in 66 patients per study group (total 132 patients, based on the use of the Wilcoxon test). In order to address potential dropouts (estimated drop-out rate 10–20%), we chose to increase the patient numbers to 75 patients in each study group. In addition, if the number of patients with secondary endpoints is sufficient, a subgroup analysis of these patients is planned.

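### The primary outcome is plural and its content shifts between sections (incidence, duration, AUC, TWA), with nothing to say which variable decides success

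*Protocol article*

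**What the plan says.** The Protocol article gives two recurring versions of the primary outcome and a third variable for the sample size.

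- **Incidence, duration and severity.** The abstract (Methods/design) says "The primary endpoint is the incidence, duration and severity of IOH", and that it is "calculated as the area under MAP < 65 mmHg and the time-weighted average (TWA) of MAP < 65 mmHg". The Study objectives ask whether the intervention "can reduce the incidence, duration, and severity of IOH in comparison with no GDT". The opening of the Discussion lists the same three.
- **Incidence and severity only.** The Primary hypothesis is that the intervention "reduces the incidence, and severity of IOH in patients undergoing major trauma and orthopedic surgery". The Outcome section agrees: "The primary outcome is the incidence and severity of IOH in patients undergoing major trauma and orthopedic surgery". It then fixes the severity measure: "The severity of IOH will be quantified using the TWA of hypotension". AUC appears there only as the numerator of TWA.
- **Sample size calculation.** The stated aim is incidence: "The aim of the study is to show the impact of non-invasive cardiac output monitoring on the incidence of IOH". The figures printed for the calculation are AUC values, 34.2 against 32.7 mmHg min.

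The Statistical analysis section assigns t or Wilcoxon tests to metric variables and Fisher's exact test to categorical ones, with a two-tailed 0.05 threshold. It does not single out a primary variable.

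**The concern.** A trial needs one stated condition under which it counts as positive. Here the same data could be read as a success or a failure depending on which component is put forward, and different sections would support different choices. There are three ways to read a plural primary, and each has a cost:

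- Any one significant component is enough. The chance of a false positive then exceeds 5%.
- Alpha is shared among the components. The sample size then gives less than the stated power.
- All components must be significant. Power then cannot exceed that of the weakest component.

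The sample size does not settle the matter, because its stated aim (incidence) and its figures (AUC) differ from each other, and neither is the severity measure in the Outcome section (TWA).

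**Working it through.** **1. The sections side by side**

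| Section | Incidence | Duration | Severity or metric |
|---|---|---|---|
| Abstract, Methods/design | yes | yes | AUC and TWA |
| Primary hypothesis | yes | no | severity, metric not named |
| Study objectives; Discussion | yes | yes | severity, metric not named |
| Outcome | yes | no | TWA |
| Sample size calculation | yes (aim) | no | AUC (figures used) |
| Statistical analysis | no variable named as primary | | |

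Even the narrowest reading, the Outcome section alone, leaves two primary quantities.

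**2. Does the plan's own sample size identify the primary?**

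The stated result is 66 per group (Wilcoxon test, alpha 0.05, power 0.95). I assume that the bracketed ranges are quartiles, which the document does not say, and take SD = width / 1.349:

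- (112.7 − 8.5) / 1.349 = 77.2 and (102 − 6.3) / 1.349 = 70.9; pooled SD 74.2.
- Standardised difference: (34.2 − 32.7) / 74.2 = 0.020.
- n per group = 2 × (1.960 + 1.645)² / 0.0202² ≈ 63,500, before any Wilcoxon correction.

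So 66 does not follow from the AUC figures under this approximation. That is a separate matter. It counts here only because the sample size cannot be used to infer which variable is primary. For step 4 I use the effect for which 66 per group gives 95% power (normal approximation): d = (1.960 + 1.645) × √(2/66) = 0.63.

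**3. Type I error if any one component counts**

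The ceiling, if the tests were independent, is 1 − 0.95^k: 9.75% for two, 14.3% for three and 18.5% for four. All these measures come from one pressure trace and are strongly correlated, so I rely on simulation instead. Null trials had 66 per arm and 3,000 trials per scenario, with Wilcoxon tests for duration, AUC and TWA, and Fisher's test for any hypotension (yes/no). The distributions are assumed. Two sets of simulations with different assumptions were run:

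| Components that may count | First set (85% or 60% of patients hypotensive) | Second set (three scenarios) |
|---|---|---|
| Incidence or TWA | 6.6%, 6.4% | 5.9–7.8% |
| Incidence, duration or TWA | not run | 6.7–9.6% |
| Incidence, duration, AUC or TWA | 8.8%, 8.0% | 6.8–10.0% |

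In the first set TWA alone rejected in 4.6% and 4.9% of trials, and Fisher's test for incidence in 2.7% and 3.4%. The Monte Carlo standard error near 6.5% is √(0.065 × 0.935 / 3000) ≈ 0.45 percentage points.

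**4. Power if alpha is split (Bonferroni)**

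Power at 66 per group = Φ(3.605 − z), where z is the two-sided critical value at 0.05/k:

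| Primaries k | Alpha each | z | Power at 66 per group | n per group for 95% |
|---|---|---|---|---|
| 1 | 0.05 | 1.960 | 95% | 66 |
| 2 | 0.025 | 2.241 | 91% | 77 |
| 3 | 0.0167 | 2.394 | 89% | 83 |
| 4 | 0.0125 | 2.498 | 87% | 88 |

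**The case against.** The strongest reply has three parts.

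- **The Outcome section is the operative definition.** It gives incidence plus TWA. AUC is only an ingredient of TWA there, and duration has no measure of its own anywhere. This stands in part: it reduces the count from four to two and the inflation to about 6–8%. It does not say which of the two decides, and it leaves the abstract, objectives and sample size section in disagreement with it.
- **Rules for sharing alpha are often left to the analysis plan, and this is a condensed article.** That is fair, and the absence of a hierarchy would not by itself be a finding. An analysis plan that is not shown could supply one, but it could not make these sections agree on what the primary outcome is.
- **The measures are so correlated that the inflation is modest.** This also stands, and is why the independence figures are only ceilings.

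A reader might be tempted to go further in three ways that the document does not support.

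- It is not true that every section describes the outcome differently. The hypothesis and Outcome section agree, as do the abstract, objectives and discussion on the three named components.
- An inflation of about 11% is reached only by adding a count of episodes, which is one possible reading of incidence and is not named as an outcome.
- The values 8.5 and 6.3 do not show that at least 75% of patients in this trial would be hypotensive. The brackets are not labelled as quartiles, the central value is called a mean, and a positive area does not establish an episode of at least one minute, which this trial requires.

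**Conclusion.** The point holds and should be fixed. The contradiction can be read from the text and needs no simulation: there are two recurring versions of the primary outcome, plus a sample size section whose stated aim and printed figures do not match.

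Its size depends on how success would be declared. If any one component may count, the excess over 5% is moderate rather than dramatic. The ranges rest on assumed distributions for duration, depth and anaesthesia time, so they indicate size and are not exact error rates. The Bonferroni losses hold at a standardised effect of about 0.63, which is implied by 66 per group and not stated in the document. If all components must succeed, the power loss cannot be calculated from what the document gives.

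The larger risk is the freedom to choose the deciding component after results are known.

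**What to change.** By a dated amendment made before any between-group comparison is seen:

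1. Name TWA of MAP below 65 mmHg, already defined in the Outcome section, as the single primary outcome in the abstract, hypothesis, objectives, Outcome and sample size sections. Test it once at two-sided 0.05.
2. Make incidence, duration and AUC secondary. Either test them in a fixed order after TWA or report them with confidence intervals only.
3. State that the existing sample size was presented on AUC figures. Restate power for TWA only with an explicit TWA assumption and its source, since the document gives no TWA mean or spread.

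Co-primary outcomes with an explicit alpha rule would also remove the defect, at the power cost shown above. TWA is preferred because its definition is already written.

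**Cost.** No new data are needed. Recruitment began in July 2024 under protocol version 1.1, so this is a formal amendment during the trial and not just a change of wording. The sponsor also gives up claiming success on another component alone.
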